### Outcome measures

#### Primary outcomes

The first primary outcome will be the clinical efficacy evaluated by the change of the Hamilton Depression Rating Scale (HAMD) with 24 items (HAMD-24), which meet the scoring criteria as follows: a total score of <8 indicates normal, a total score of ≥8 indicates different levels of depressive symptoms, and a higher score indicates more severe depression. As an other-report and screening questionnaire, individuals with depression will be diagnosed using this scale before enrollment. A HAMD-24 score ≥ 8 will be considered as one of the inclusion criteria in this study. The HAMD-24 score will be assessed at baseline and at 4 weeks.

The second primary outcome will be the change of rs-fMRI in probing possible central mechanisms. Functional neuroimages will be collected using a 3.0 Tesla Philips Ingenia CX MRI system in our hospital. Rs-fMRI data will include three-dimensional T1 weighted structural imaging with a FSE sequence and BOLD imaging with a SE-GRE-EPI sequence for 7.5 min, covering the whole brain. The parameters for 3D-T1* imaging will include a slice thickness of 1 mm, a TR/TE of 9.8 ms/4.6 ms, an FOV of 240× 240 × 192 mm^3^, a flip angle of 8^°^, a matrix of 240 × 240, an in-plane resolution of 1 × 1 × 1 mm^3^, and 192 layers. The parameters for BOLD imaging will include a slice thickness of 4 mm, a TR/TE of 2,000 ms/30 ms, a flip angle of 90^°^, a matrix of 64 × 64, an FOV of 192 × 192 × 140 mm^3^, 35 layers, and 320 time points.

The fMRI data will be preprocessed with the DPABI toolkit.^1^ Preprocessing steps will mainly include slice timing, realignment, regression, normalization, smoothing, detrending, and filtering, similar to a previous study (25).

Regional homogeneity (ReHo), a classical and commonly used analysis in rs-fMRI, provides an indirect measure of the temporal coordination of spontaneous neural activity within a specific region of the brain. Kendall’s coefficient concordance (KCC) can quantify the similarity of a number of time series between a given voxel and the nearest neighbors in a voxel-wise way, using the REST software in Matlab. Specifically, each voxel in the entire brain is compared to its nearest 26 voxels. Subsequently, an individual ReHo image is obtained based on the KCC value, which is computed for each voxel. When normalization is performed, an average ReHo image is achieved by dividing each KCC value by the mean KCC value of the entire brain. The KCC-ReHo value ranges from 0 to 1, and higher values indicate stronger consistency in temporal activity among neighboring voxels and reflects the synchronization of local neuronal activity within the brain.

Amplitude of low frequency fluctuations (ALFF) is another alternative and reliable index of rs-fMRI signals. It has been suggested that it indirectly reflects the regional intensity of spontaneous brain activity in the power spectrum of low-frequency (0.01–0.08 Hz) of the resting-state BOLD signal in the brain, is closely associated with the neural activities, and is physiologically meaningful. ALFF can be divided into distinct frequency bands including slow-5 (0.01–0.027 Hz) and slow-4 (0.027–0.073 Hz). Evidence indicates that fractional ALFF (fALFF) in slow-5 and slow-4 bands could be more sensitive in revealing the features of spontaneous activities in brains compared to ALFF.

The obtained ReHo and fALFF value will be analyzed using MATLAB and SPM12 software. The cluster sizes, active brain regions, and their MNI coordinates will all be noted. In addition, ICA using the GIFT software package^2^ will be used to analyze the data after smoothing preprocessing. This will obtain the spatial distribution pattern of the DMN based on the estimated components, using an informax algorithm during spatial ICA. The results of brain network analysis will be presented in BrainNet Viewer. The abovementioned scanning and analysis will be carried out at baseline and at 4 weeks.

The acceptability questionnaire is well-designed to assess the acceptability of EA and rTMS treatment, determined through patients’ subjective feelings. It involves three levels: “fully accepted,” “acceptable,” and “not acceptable.” The acceptance rate is calculated via the number of “fully accepted” and “acceptable” subjects. The effective rate is the ratio of effective people to total people. A higher rate means a better acceptability. The acceptability rates will be measured at 4 weeks.

### Sample size

Sample size was calculated based on the literature change of HAMD-24 scores as a primary outcome measure, using the following formula for a comparison between the two groups:

$$n_{2}=\frac{k+1}{k}\frac{{\left(Z_{\alpha /2}+Z_{\beta }\right)}^{2}\sigma^{2}}{\delta^{2}}$$

$$n_{1}=kn_{2}$$

A two-sample *t* test was selected in this research; σ represents the difference between the standard deviations of the HAMD-24 scores at 4 weeks in the experimental group (EA + rTMS) and the control group (rTMS) and δ indicates the difference between the means of the HAMD-24 scores in the two groups. G·Power software (version 3.1.9.7) was used for sample size calculation. According to the results from existing published literature (29), the mean (standard deviation) of the HAMD-24 at baseline before treatment was 27.52 (2.06) for the experimental group and 27.84 (2.55) for the control group. The mean (standard deviation) of the HAMD-24 after 4 weeks of treatment was 11.06 (3.37) for the experimental group and 14.13 (3.15) for the control group. To achieve a power (1 − β) of 0.90 at an alpha level of 5% (2-tailed) and a k value of 1, it was estimated that approximately 25 individuals will be needed in each group. Anticipating a 20% drop-out rate, a total of 64 subjects will be recruited to take part in the study, with 32 patients in each group. Moreover, 10 healthy subjects will be involved in the study, from which normal MRI data will be collected, without randomization and intervention.

### Randomization and allocation concealment

Eligible patients who meet the criteria will be randomly assigned to the experimental or control group at a ratio of 1 to 1, with a randomized block design, namely, A and B. Independent random sequences will be computer-generated and retained by the principal investigator (PI) ([name]), who will not be involved in outcome measurement or data analysis. Therapists will receive each subject’s random number and group assignment through consecutive opaque envelopes. Before participation, the subjects will be informed that they have an equal opportunity to be allocated in either the experimental or control group.

### Blinding

For blinding, because the intervention style will seem dissimilar between EA + rTMS and single rTMS, an open label design will be adopted. However, all subjects will be treated separately to prevent communication in different rooms. Moreover, the MRI scan technicians, outcome assessors, data entry clerks, data administrators, and data statisticians will all be blinded to the grouping with labels A and B.

### Informed consent

The informed consent form has been approved by the Medical Ethics Committee of the Affiliated Drum Tower Hospital, Medical School of Nanjing University (version 1.1). Subjects will be informed of all aspects of the trial, which include the study background and purpose, inclusion and exclusion criteria, available treatments and alternatives, and benefits and harms, as well as rights and duties of the participants. More importantly, informed consent will be obtained from each patient and healthy person before grouping. If patients drop out at any time during the study, the collected data will still be retained for mITT analysis.

### Safety monitoring

Safety indexes will include records of physical examination/vital signs, clinical laboratory tests, and adverse events (AEs) during treatment. If any AEs happen, the investigator will complete the AE form in case report form (CRF), including the onset time, related symptoms/signs, duration, abnormal laboratory examinations, treatment, and prognosis. Then, the investigator will need to evaluate the relationship between the AEs and EA + rTMS based on the form presented in Table 1.

### Data collection and management

During the 4 week clinical study, patients will need to receive EA + rTMS or rTMS alone for 4 consecutive weeks, and two visits will be needed to complete fMRI scans and a series of scales at baseline and at 4 weeks. After screening, the raw data will be comprehensively documented in paper CRF (pCRF) within 2 days and electronic CRF (eCRF) will be completed in the electronic data capture (EDC) system^3^ within 14 days. Nobody, except for the PI ([name]) and clinical research associates (CRA) ([name]) will be eligible to review the database. The raw pCRF documents will be kept in the archives of the Affiliated Drum Tower Hospital, Medical School of Nanjing University for more than 5 years after study completion.

### Statistical analysis

All data analyses of this study will be done by an independent statistician ([name]) from University of Cape Town in South Africa using IBM SPSS Statistics for Windows, version 25.0 (IBMCorp., Armonk, N.Y., USA). The modified intention to treat (mITT) principle will be applied for all outcomes in the full analysis set. If the endpoints are missing, the last-observation-carried-forward (LOCF) method will be used according to mITT analysis. The mean, standard deviation (SD), minimum (min), maximum (max), and median will be reported for the quantitation data. The frequency (*n*) and corresponding percentage (%) will be given for the enumeration data. For intra-group comparisons, Student’s paired t test or Wilcoxon signed rank test will be used, and the chi-squared test will be utilized for qualitative indexes. For inter-group comparisons, independent-sample T test or Mann–Whitney U test will be applied. Pearson correlation coefficient or Spearman correlation coefficient will be used for correlation analysis between scale scores and fMRI data. An alpha level of 5% (2-tailed) will be selected.

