### Compliance and discontinuation

Based on the above-mentioned withdrawal criteria, if a participant receives more than six EA/rTMS sessions, this will be considered a valid case to generate reliable data. For patients who drop out without enough sessions, their last visit data will be used for result analysis.

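### With HAMD-24 taken only at baseline and week 4, LOCF scores every missing outcome as zero change, and the stated 90% power does not hold if the planned 20% drop-out means missing week-4 scores

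*Protocol article*

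**What the plan says.** All from the protocol article.

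- **Statistical analysis:** mITT applies to all outcomes, and "If the endpoints are missing, the last-observation-carried-forward (LOCF) method will be used according to mITT analysis". Groups are compared with an independent-sample t test or a Mann-Whitney test. No rule for choosing between them is given.
- **Compliance and discontinuation:** "For patients who drop out without enough sessions, their last visit data will be used for result analysis".
- **Informed consent:** data collected from patients who drop out are kept for the mITT analysis.
- **Data collection and management:** "two visits will be needed to complete fMRI scans and a series of scales at baseline and at 4 weeks". Table 1 and Primary outcomes give the same two time points for HAMD-24. No interim or early-termination HAMD-24 is scheduled.
- **Abstract:** the primary outcome is the change in HAMD-24 from baseline to week 4.
- **Sample size:** the baseline mean (SD) "was 27.52 (2.06) for the experimental group and 27.84 (2.55) for the control group", and the week-4 mean (SD) "was 11.06 (3.37) for the experimental group and 14.13 (3.15) for the control group". About 25 per arm are needed, and "Anticipating a 20% drop-out rate, a total of 64 subjects will be recruited to take part in the study".

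**The concern.** LOCF normally carries forward some post-baseline value. Here there is none, so a missing week-4 score becomes the baseline score and the patient enters the primary comparison as a complete non-responder. Both arms are expected to improve by about 14 to 16 points, so these zeros lie far from every other value. They shrink the mean difference and roughly double the standard deviation.

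The sample size does not allow for this. Going from 25 to 32 per arm (25/0.8, rounded up) is right if drop-outs are removed and 25 completers remain. The analysis rules keep them in at zero change, so the power statement and the analysis rule describe two different analyses.

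The estimate also becomes sensitive to differences in drop-out. Each extra percentage point missing in one arm lowers that arm's mean improvement by about 0.14 to 0.16 points, whatever the treatment does.

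**Working it through.** **1. Reproduce the stated sample size.** The difference in week-4 means is 14.13 − 11.06 = 3.07. The pooled SD is √((3.37² + 3.15²)/2) = 3.26, so d = 0.941. The plan states: "To achieve a power (1 − β) of 0.90 at an alpha level of 5% (2-tailed) and a k value of 1". With the noncentral t, 24 per arm gives 89.1% and 25 gives 90.3%. Then 25/0.8 = 31.25, rounded up to 32 per arm and 64 in total. The stated figures reproduce, on the week-4 score.

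**2. Inputs for LOCF.** Mean falls are 27.52 − 11.06 = 16.46 (EA + rTMS) and 27.84 − 14.13 = 13.71 (rTMS), a difference in change of 2.75. The change-score SD needs the baseline-to-week-4 correlation r, which the article does not give. I assume r = 0.5 and show 0 to 0.7. At r = 0.5 the change SDs are √(2.06² + 3.37² − 2.06 × 3.37) = 2.94 and √(2.55² + 3.15² − 2.55 × 3.15) = 2.90. Missingness is taken as unrelated to outcome.

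**3. LOCF mixture on change, fraction p missing in each arm.** The mean is (1 − p)μ and the variance is (1 − p)s² + p(1 − p)μ². At p = 0.2, r = 0.5:

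- means 0.8 × 16.46 = 13.17 and 0.8 × 13.71 = 10.97; difference 2.20
- SDs √(0.8 × 2.94² + 0.16 × 16.46²) = 7.09 and √(0.8 × 2.90² + 0.16 × 13.71²) = 6.07; pooled 6.60
- d = 2.20/6.60 = 0.333; t-test power at 32 per arm 25.9%

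**4. LOCF mixture on the week-4 score, p = 0.2.** The means are 0.8 × 11.06 + 0.2 × 27.52 = 14.35 and 0.8 × 14.13 + 0.2 × 27.84 = 16.87, a difference of 2.52. The SDs are 7.30 and 6.27, pooled 6.80. Power is 30.8%.

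**5. Power at 32 per arm.** The t-test figures under LOCF are analytic. Mann-Whitney and observed-only figures are simulated.

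| Scenario | t test, LOCF | Mann-Whitney, LOCF | t test, observed only |
|---|---|---|---|
| 20% missing, change, r = 0 | 23% | 37–38% | 68% |
| 20% missing, change, r = 0.5 | 26% | 60% | 91% |
| 20% missing, change, r = 0.7 | 27% | 75–76% | 98% |
| 20% missing, week-4 score | 31% | 60% | about 90% (25 completers, step 1) |
| 10% missing, change, r = 0.5 | 45% | 81% | 94% |
| 10% missing, week-4 score | 51% | 81% | – |

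At 10% missing, the change-score range over r = 0 to 0.7 is 38% to 49% for the t test and 56% to 93% for Mann-Whitney. These figures give each patient an independent chance of being missing. With exactly 6 or 7 missing in each arm, t-test power is lower, about 2% to 15%.

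**6. No true effect, equal drop-out (20% in both arms).** Both tests reject in about 5% of simulated trials.

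**7. No true effect, unequal drop-out (hypothetical).** Both arms follow the control course, a fall of 13.71.

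- 10% vs 30%: spurious difference 0.20 × 13.71 = 2.74. At r = 0.5 the false rejection rate is about 42–45% with the t test and 27–29% with Mann-Whitney.
- 15% vs 25%: spurious difference 0.10 × 13.71 = 1.37, with false rejection of about 14% and 10%.
- Gap that creates the full planned week-4 difference: 3.07/13.71 = 22.4 percentage points, about 9% vs 31%.

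The bias can also run the other way. With the planned effect real and 25% missing on EA against 15% on control, the expected difference is 0.75 × 16.46 − 0.85 × 13.71 = 0.69.

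**The case against.** **The rank test might be used.** A spike at zero beside values near 14 to 16 is plainly non-normal. In simulation at 20% missing, a Shapiro-Wilk check rejected normality in at least one arm in essentially every trial. If the choice turns on normality, Mann-Whitney would apply and power would be nearer 60% than 26%. This stands, and a single figure of 26% would mislead. At 10% missing and high correlation the rank test can even reach 90%. At the planned 20% it does not reach 90% anywhere in the range examined.

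**Drop-out is not the same as a missing score.** The Drop-out criteria include patients with too few sessions, with other treatments or with missed MRI scans. Some of them may still have a week-4 HAMD-24, which LOCF would not touch. This stands, and makes 20% missing close to the worst case for the stated rate.

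**mITT is undefined in the article and might require a post-baseline value.** Possible, but the sections on compliance and on consent keep drop-outs in. If patients without a week-4 HAMD-24 were excluded, LOCF would have nothing to fill for that outcome.

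**Readings that go too far.** A reader might infer that the primary test is invalid under the rule. The article does not support that: with equal drop-out, type I error stays near 5%, and no drop-out rates by arm are given, so 10% vs 30% is a constructed case. A reader might also take 2.75 as the planned difference, but the sample size rests on 3.07 at week 4. Finally, a reader might infer that baseline brain images will be carried forward. The article applies mITT to all outcomes but nowhere describes imputing images, so this needs clarifying and is not an established error.

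**Conclusion.** Wrong as written. The LOCF rule turns every missing week-4 HAMD-24 into zero change and contradicts a sample size that treats drop-outs as removed. That much follows from the text alone.

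The size of the loss depends on assumptions: 20% of week-4 scores missing in both arms, missingness unrelated to outcome, and a correlation the article does not give. On those terms, power at 32 per arm is about 23% to 31% with the t test (change score over r = 0 to 0.7, or week-4 score). With Mann-Whitney it is about 60% at r = 0.5, and about 37% to 76% over the range. Not all of the shortfall at low correlation is due to LOCF: at r = 0 the observed-only t test on change has only 68%. At r = 0.5, and on the week-4 score, analysing observed values keeps about 90%, so there the loss comes from the imputation.

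Bias from unequal drop-out is a risk, not a forecast. Patients are unblinded and only one arm has added needling, so equal drop-out cannot be taken for granted.

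**What to change.** - Remove LOCF as the primary rule from Statistical analysis, and the matching last-visit rule from Compliance and discontinuation.
- Seek the week-4 HAMD-24 from every randomised patient, whatever the treatment status.
- Make the primary analysis a baseline-adjusted comparison (ANCOVA) of observed week-4 scores, or use multiple imputation by arm with baseline HAMD-24, NIHSS and sessions received. A mixed model adds little, because with one post-baseline visit it is essentially the same as the ANCOVA.
- Keep zero-change imputation as a labelled sensitivity analysis, with a delta-adjusted imputation beside it.
- State that LOCF does not apply to the rs-fMRI outcomes.

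The cost is revised analysis wording, settled before the database is locked, and a few extra week-4 contacts. The downside is that the primary analysis then rests on a missing-at-random assumption, which the sensitivity analyses probe. The figure of about 90% for observed data likewise assumes that drop-out is unrelated to outcome.

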**Methods:**

In this randomized, controlled, open-label trial, 64 patients with PSD will be randomly allocated into the experiment group (*n* = 32) or control group (*n* = 32). The experiment group will receive EA and MRI-navigated rTMS and the control group will receive MRI-navigated rTMS treatment, in 12–20 sessions over 4 weeks. In addition, 10 healthy people for fMRI scanning will be recruited as a healthy control group without any intervention. The primary outcome will be the change from baseline in the Hamilton Depression Scale-24 item (HAMD-24) scores at week 4. The primary analysis of the central mechanism will mainly involve cortical morphology, local spontaneous brain activity, and the default mode network (DMN) functional connectivity based on fMRI at 0 and 4 weeks. Secondary outcomes will include the neuro-patho-physiological and quality of life changes in cortical excitability, determined using the motor evoked potential test (MEP), National Institutes of Health Stroke Scale (NIHSS), EuroQol Five Dimensions Questionnaire (EQ-5D) Scale, Modified Barthel Index (MBI) Scale, and Health Scale of Traditional Chinese Medicine (HSTCM). Additional indicators will include the Acceptability Questionnaire and Health Economics Evaluation (cost-effectiveness analysis) to assess the acceptability and economic practicality of the treatment under study. Outcomes will be assessed at baseline and post intervention.

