### Inclusion criteria

(1) Inclusion criteria for patients include the following:Meet the diagnostic criteria for first onset stroke within 6 months, based on the Chinese Guidelines for Diagnosis and Treatment of Acute Ischemic Stroke 2018 (24).Aged 40–75 years.Right-handed.Single infarct in basal ganglia (volume: 3–5 cm).Motor evoked potential (MEP) could be recorded by bilateral primary motor cortex (M1) stimulation.National Institutes of Health Stroke Scale (NIHSS) score < 6.Hamilton Depression Scale-24 items (HAMD-24) score > 8.Clear consciousness, no hearing and visual impairment, and cooperative physical examination (Glasgow Coma Scale (GCS) score > 8).Complete the screening and voluntarily sign the informed consent form.(2) Inclusion criteria for healthy subjects include the following:Healthy subjects, aged 40–75 years.Right-handed.HAMD-24 score < 8.Voluntarily sign the informed consent form.

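### The between-arm test for HAMD-24 is an unadjusted t test or Mann–Whitney test with no rule for choosing; one baseline-adjusted ANCOVA would be at least as efficient over the plausible range and would hold the planned power for the change endpoint

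*Protocol article*

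**What the plan says.** The abstract (Methods) defines the endpoint: "The primary outcome will be the change from baseline in the Hamilton Depression Scale-24 item (HAMD-24) scores at week 4". The Primary outcomes section also describes it as a change and adds: "The HAMD-24 score will be assessed at baseline and at 4 weeks". Both values are therefore planned for each randomised patient.

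For the comparison of arms, the Statistical analysis section has one sentence for all quantitative outcomes: "For inter-group comparisons, independent-sample T test or Mann–Whitney U test will be applied". It continues with "An alpha level of 5% (2-tailed) will be selected". No covariate, adjusted model or criterion for choosing between the two tests appears anywhere in the article.

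The Sample size section is built on a t test: "A two-sample *t* test was selected in this research". Its target is given as "To achieve a power (1 − β) of 0.90 at an alpha level of 5% (2-tailed) and a k value of 1", and its effect comes from week-4 scores in a published study, where the mean (SD) "was 11.06 (3.37) for the experimental group and 14.13 (3.15) for the control group". The baseline values quoted from the same study are 27.52 (2.06) and 27.84 (2.55).

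On severity at entry, the Inclusion criteria give only a lower limit: "Hamilton Depression Scale-24 items (HAMD-24) score > 8". The Randomization section mentions blocks but no stratification factor.

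**The concern.** Two things are fixed less well than they could be.

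The first is efficiency. A t test on change uses baseline with a slope of exactly 1. If the true regression slope of week-4 score on baseline is different, the change score either over-corrects or under-corrects, and its variance is larger than it need be. ANCOVA estimates the slope at the cost of one degree of freedom. Because the trial was sized on week-4 scores but its endpoint is change, the planned 90% power does not automatically carry over to the stated endpoint.

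The second is that two tests are named without a rule. They target different quantities: the t test a mean difference, Mann–Whitney a shift in rank order. Until one is chosen, the primary p-value and effect measure are not pinned down.

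At stake are some power and the clarity of the primary result. The validity of the trial is not in question.

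**Working it through.** **Inputs from the Sample size section.** Week-4 SDs 3.37 and 3.15; baseline SDs 2.06 and 2.55; 25 evaluable per arm; two-sided 5%. The baseline to week-4 correlation r is not in the protocol, so it is assumed over a range.

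- Pooled week-4 SD: s1 = √[(3.37² + 3.15²)/2] = 3.262
- Pooled baseline SD: s0 = √[(2.06² + 2.55²)/2] = 2.318
- Week-4 difference: 14.13 − 11.06 = 3.07
- Difference in change: (27.52 − 11.06) − (27.84 − 14.13) = 16.46 − 13.71 = 2.75

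**Plan's own figure.** Standardised effect 3.07/3.262 = 0.941. The normal approximation gives 24 per arm. The exact (noncentral t) calculation gives 25, with power 0.903. Allowing for 20% dropout, 25/0.8 = 31.25, rounded up to 32. The stated 25 and 32 per arm are reproduced, for a t test on week-4 scores.

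**Formulae.** SD of change = √(s0² + s1² − 2·r·s0·s1). Residual SD under ANCOVA = s1·√(1 − r²), with one fewer degree of freedom. Each goes into the exact two-sample t power at 25 per arm.

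**Difference 3.07:**

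| r | SD, change | SD, ANCOVA | Power, change t test | Power, ANCOVA |
|---|---|---|---|---|
| 0 | 4.00 | 3.26 | 0.757 | 0.903 |
| 0.3 | 3.39 | 3.11 | 0.881 | 0.927 |
| 0.5 | 2.91 | 2.82 | 0.955 | 0.964 |
| 0.7 | 2.33 | 2.33 | 0.995 | 0.995 |

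**Two landmarks.** The change score is as precise as the raw week-4 score when s0² = 2·r·s0·s1, that is r = s0/(2·s1) = 2.318/6.524 = 0.355. Below about 0.36 the change-score test falls short of the planned power. The ANCOVA slope r·s1/s0 equals 1 when r = s0/s1 = 0.711, and there the two methods have the same variance.

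**Difference 2.75** (the published difference in change), change t test against ANCOVA: 0.663/0.831 at r = 0, 0.803/0.864 at r = 0.3, 0.906/0.921 at r = 0.5, 0.983/0.983 at r = 0.7. With this smaller effect neither method reaches 90% at low r, but the ordering is the same.

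**If the baseline spread is wider (assumption).** Take SD 4 at both visits and difference 2.75. The variance ratio of ANCOVA to change is (1 + r)/2, so variance is 35%, 25% and 15% smaller at r = 0.3, 0.5 and 0.7. Power is 0.521/0.704, 0.663/0.785 and 0.868/0.915.

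**Choice of test, by simulation** (normal data, plan SDs, 25 per arm, 8,000 runs per setting). At difference 3.07, Mann–Whitney on change had power 0.863 against 0.925 for ANCOVA at r = 0.3, and 0.945 against 0.961 at r = 0.5. If the smaller of the t and Mann–Whitney p-values were always taken, the type I error was 5.4% to 6.2%, against about 5% for one fixed test. The week-4 t test, the change t test and ANCOVA all estimated the same mean difference, about 3.07 to 3.09.

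**The case against.** The strongest reply is that nothing here is wrong. In a 1:1 randomised trial, a two-sample t test on change is unbiased and controls alpha, and the endpoint already subtracts baseline. This stands. A reader might infer that the plan ignores baseline or that its primary test is invalid; the change-from-baseline definition in the abstract and the Primary outcomes section rules out both.

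Second, the gain is modest on the plan's own SDs. It is about 5 points of power at r = 0.3 (6 at difference 2.75), about 1 point at r = 0.5, and nil near r = 0.7. This stands too. Much larger gains, such as 0.52 to 0.70, come only from the assumed SD of 4. The article gives a lower entry limit but no expected spread, so wide baseline variation is possible but not established.

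Third, a reader might infer that the test will be picked after looking at the data. The text does not say so. It gives no rule, and the Sample size section points to a t test. A statistical analysis plan that is not shown may settle the choice between the two tests. A baseline-adjusted primary model, though, would be a change from the method this article states.

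Fourth, one linear model should not be imposed on every secondary outcome. NIHSS must be below 6 at entry, so its scores are small bounded integers, and a linear model is not obviously better there. This is accepted.

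**Conclusion.** The point holds as an improvement in efficiency and pre-specification. With the plan's SDs, 25 per arm and a difference of 3.07, ANCOVA keeps the planned 90% power at every non-negative r. The t test on change has 0.76 at r = 0 and reaches the planned power only from r of about 0.36.

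The size of the gain rests on r, which the protocol does not give. It would be larger if this trial's baseline SD exceeds the planning value of 2.32, which is an assumption. The guarantee of 90% is tied to the 3.07 difference; at 2.75, ANCOVA has 0.83 at r = 0 and 0.86 at r = 0.3. The planned 32 per arm need not rise at the planned difference.

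**What to change.** Before unblinding, name a single primary analysis: ANCOVA of week-4 HAMD-24 on arm with baseline HAMD-24 as covariate, reporting the adjusted mean difference with its 95% confidence interval. With baseline in the model, using change instead of week-4 score as the response gives the same treatment estimate, so the stated endpoint is respected. Keep any rank-based test as a named sensitivity analysis.

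Baseline adjustment may also be used for continuous secondary scales where a linear model suits the data. Bounded scores such as NIHSS need not use it.

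The cost is a change of wording and one degree of freedom. HAMD-24 is already scheduled at both visits, the software named in the plan fits the model, and no extra patients or data are needed.
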